### Study population and recruitment procedure

A total of 90 female CFS patients and 30 age and education matched female healthy controls will be recruited from the ECCF of the radboudUMC in Nijmegen, the Netherlands. Only female patients are included for homogeneity. Patients that are referred to the ECCF of the Radboudumc, are diagnosed with CFS according to the US Centers for Disease Control and prevention (CDC) consensus-criteria ([66]; Reeves et al., [2]), and scoring 40 or higher on the subscale fatigue severity of the Checklist Individual Strength (CIS) and have a total score of 700 or higher on the Sickness Impact Profile 8 (SIP8) will be informed about the study by their treating psychologist during their first intake session at the ECCF. If the patients agree, they will receive an information folder. The investigator will call the patients after a one week reflection period to answer any further questions and to ask for participation. If willing to participate, and meeting all in- and exclusion criteria (Table 1), patients will be invited for the first testing day at the Donders institute for brain cognition and behavior. Age and education matched female healthy controls will be recruited though advertisements and through flyers in the patients folder. Interested healthy controls will receive an information folder and the recruitment procedure will follow the same steps as described above. Written informed consent will be given at the first session day. Randomization of patients will take place after the first session day. The Mini-international Neuropsychiatric Interview (M.I.N.I) will be used to rule out any current psychiatric disorders.

**Table 1 Tab1:** Inclusion and exclusion criteria

Inclusion criteria	
1.	Female
2.	Age between 18 and 55 years
Additional inclusion criteria for CFS patients	
1.	CFS diagnosis according to the CDC-criteria ([66]; Reeves et al., [2]);
2.	Fatigue severity subscale (CIS) score ≥40
3.	Severely disabled, defined by scoring ≥ 700 on the Sickness Impact Profile (SIP)
4.	Eligible for treatment with CBT
Additional inclusion criteria for healthy controls	
5.	Fatigue severity subscale (CIS) score ≤ 35
Exclusion criteria	
1.	Current use of psychotropic medication (e.g. antidepressants)
2.	Contra-indication for MR-examinations (e.g. claustrophobia)
3.	Abnormal hearing or (uncorrected) vision
4.	Insufficient command of the Dutch language to fill out questionnaires, understand task instructions or perform the neuropsychological tests
5.	Restricted function of the right hand that confounds handgrip performance for the fMRI tasks
Additional exclusion criteria for healthy controls	
6.	Current psychological or psychiatric disorder^a,b^
7.	(History of) alcohol or substance abuse^a^
8.	Severe obesity (BMI ≥ 40)^a^
9.	Chronic disease or pain condition (e.g. rheumatoid arthritis)
10.	Current acute pain condition

^a^these criteria are part of the CDC criteria for CFS

^b^as revealed by the Mini International Neuropsychiatric Interview (M.I.N.I.)

### Intervention

CBT for CFS (Heins et al., [67]; Wiborg et al., [9]) aims at recovery, meaning that the CFS patient is no longer severely fatigued and disabled by the fatigue, by changing cognitions and behaviors assumed to perpetuate the symptoms. Previous trials have repeatedly demonstrated that CBT for CFS leads to a significant reduction of fatigue and disability ([68]; Prins et al., [69]; White et al., [6]; White et al., [70]; Wiborg et al., [9]) and to recovery in a subset of patients (Knoop et al., [5]; White et al., [6]). CBT treatment will be given by trained cognitive behavioral therapists at the ECCF of the radboudUMC in Nijmegen, the Netherlands. Treatment consists of 12–14 individual sessions with a trained cognitive behavioral therapist within a period of approximately 6 months. The treatment starts with explanation of the cognitive behavioral model of CFS and goal setting. Patients formulate their goals in concrete activities they will do when they are no longer bothered by fatigue, e.g. resumption of work or study. Then, patients will learn to regulate their sleep-wake cycle by maintaining fixed bedtimes and no longer sleep or lie down during the day. Once the sleep-wake cycle is regulated, patients will start with a graded activity program consisting of a graded increase in walking of cycling activities. Based on their physical activity patterns, relative active patients will first learn to better divide activities across the day before starting with the graded activity program and low active patients will start directly with the graded activity program. Dysfunctional fatigue-related cognitions, e.g. catastrophising in response to fatigue, low self-efficacy and increased focus on symptoms are challenged continuously throughout the intervention. When activity levels are increased and patients attain the belief that they have potential to be more active, they start with realization of their prior set goals. The last part of the intervention aims at reappraisal of fatigue as a normal sensation and prevention of relapse.

### Outcome measures

#### Primary clinical outcome measures

Fatigue severity will be measured using the subscale fatigue severity of the CIS consisting of 8 items scored on a 7-point Likert Scale with a total score ranging between 8–56 (Vercoulen et al., [71]). Higher scores indicate higher levels of fatigue. This questionnaire has been validated extensively in patients with CFS ([72, 73]; Vercoulen et al., [71]; Vercoulen et al., [42]). Following previous reports (Prins et al., [69]; Wiborg et al., [10]) we will use cut-off score of ≥ 40 for inclusion of severely fatigued CFS patients.

Successful treatment is defined by a clinically significant improvement on the CIS sub-scale fatigue severity, i.e. scoring lower than 35 and a reliable change index of >1.96 on the CIS subscale fatigue (Knoop et al., [74]). The cut-off score of 35 has frequently been used as a criterion to indicate clinically relevant fatigue in clinical studies (Knoop et al., [5]; Wiborg et al., [75]).

Functional impairment will be measured in CFS patients using the Sickness Impact Profile 8 [76]. The SIP8 contains 85 statements about health-related dysfunction in 8 areas domains (home management, ambulation, mobility, intellect, social interactions, sleep/rest behaviour, recreation and work). In completing the SIP, the patient is asked to check only those statements that she is sure describe her on a given day and are related to her health. The eight subscales are added to provide one weighted score of disability (SIP8 total, range 0–5799) (Knoop et al., [5]; Prins et al., [69]; Wiborg et al., [9]). Higher scores indicate higher levels of experienced disabilities. Functional impairment will be defined as a SIP score higher than 700.

#### Secondary clinical measures

Fatigue related cognitions and behaviours, physical and social functioning are assessed using questionnaires as part of the clinical routine of the ECCF. A selection of these questionnaires will also be assed in the healthy control group and include the RAND-36 (Stewart et al., [77]; Ware and Sherbourne, [78]), the Beck depression Inventory (BDI) [79], the Symptom Checklist 90 (SCL-90) (Arrindell and Ettema, [80]), the Fatigue Quality List (KWAMOE) [81], the self efficacy scale fatigue (SES) (Prins et al., [69]; Vercoulen et al., [71]; Wiborg et al., [9]) and the Adjusted Physical Activities Rating Scale (PARS) (Vercoulen et al., [82]). In addition, the attention Control Scale questionnaire (ACS)(Derryberry and Reed, [83]) will be assessed in all subjects. During each test day, state changes in fatigue and mood will be assessed using the profile of moods (POMS) questionnaires (McNair et al., [84]) at 3 time points in both patients and healthy controls.

### Physical activity

Previous work in both humans[85] and animals (Praag, [86]) suggest a possible link between physical exercise and neurogenesis. Accordingly, given that graded increase of physical activity levels is an important part of the CBT program, we will also assess physical activity levels. As in the previous reports [13, 14], physical activity levels will be assessed in all participants, over a period of two weeks preceding both test sessions using an actometer. The actometer is a motion-sensitive device, worn at the ankle, which can register and quantify human physical activity (Werf et al., [44]).

### Neuropsychological testing

To be able to replicate previous reported correlations between grey matter volume changes and neuropsychological performance [14] we will assess two tasks of cognitive speed: the digit symbol substitution test of the Dutch Wechsler Adult Intelligence Scale (Stinnissen J et al., [87]) and a choice reaction time task ([14]; Vercoulen et al., [42]). Additionally, working memory capacity will be assessed with the digit span of the Dutch Wechsler Adult Intelligence Scale (Groth-Marnat, [88]; Stinnissen J et al., [87]) and intelligence/education level will be determined with the Dutch adult reading test (Schmand et al., [89]).

### Structural neuroimaging measures

To investigate changes in brain anatomy and metabolism, several MR-measurements will be obtained on a 3-Tesla SIEMENS MAGNETON skyra MRI scanner. To investigate global and regional grey and white matter changes high resolution anatomical images will be obtained using a T1 weighted magnetization-prepared rapid gradient-echo (MP-RAGE) sequence (TR\TE: 2300\3.03 ms, flip angle = 8°, 192 sagittal slices, FoV: 256 × 256 mm, voxelsize: 1 mm^3^, slice thickness: 1.00 mm). To investigate the microstructural properties of white matter pathways in the brain, diffusion tensor imaging (DTI) scans will be assessed (TR = 8200 ms, TE = 89.0 ms, voxel size: 2.2 × 2.2 × 2.2 mm, FOV 220 mm, 64 slices, slice thickness: 2.2 mm). Brain metabolite changes will be assessed using single voxel proton magnetic resonance spectroscopic (MRS) imaging (TR = 1500 ms, TE = 30 ms, and 64 averages). MRS spectra will be obtained from two voxels (10 × 20 × 30 mm): One voxel placed in the left middle frontal gyrus, corresponding to the previous reported region of CBT-associated grey matter changes in CFS patients [14] and one voxel placed in the left calcarine gyrus (i.e.primary visual cortex) to assess regional specificity of the changes.

### Functional MRI

To explore task-dependent functional MRI will be assessed using a multi echo, T2*-weighted, gradient-echo planar imaging (EPI) sequence (TR = 2190 ms, TE = 9.0/19.28/29.56/39.84 ms, flip angle = 90°, 36 axial slices aligned with AC-PC plane, slice-matrix size = 64 × 64, slice thickness = 3.0 mm, slice gap = 0.3 mm, FOV = 212*212 mm). Two different tasks will be employed.

With the first task, we will assess alterations in brain activation patterns in anticipation of effortful physical exertions and in response to task-feedback about these exertions. Participants are instructed to prepare and then squeeze quickly in a hand grip up to a certain level indicated by a cue. Cues will indicate to squeeze 30, 50 or 70 % of their maximal voluntary contraction (MVC). MVC will be calibrated before and after the task to assess (change in) physical ability. Subjective experience of fatigue and effort will be assessed before and after the task. Visual feedback is provided after the squeeze and will indicate whether the squeeze was “correct”, “too little” or “too much”. Neural outcome measure is the Blood Oxygen Level Dependent (BOLD) contrast during task performance. Behavioral output is the squeezed force. We will assess the hypothesis that, compared with healthy controls, CFS patients will show alterations in neural response to “too much” and “too little” and that these alterations will vary as a function of effort level. We expect that these alterations will normalize after successful treatment. In addition, neural responses during effort anticipation will be explored.

With the second task, we will assess alterations in neural activation patterns during effort avoidance learning using an adapted version of the salience attribution task (Roiser et al., [52]; Roiser et al., [53]). In this task participants learn to reduce the effort level of handgrip contractions by responding sufficiently quickly to a target presented after a cue. The cues have two dimensions (shape and color) that provide information about the probability of the occurrence of the effortful handgrip contractions. One dimension is predictive for the outcome, signaling the occurrence of the effortful handgrip contractions with 80 % and 20 % certainty. The other dimension is non-predictive for the outcome, signaling the occurrence of the effortful handgrip contractions with 50 % certainty for both cues. When effortful outcomes occur, the required effort level of the handgrip contraction is reduced as a function of reaction time to the target. Thus, the faster the subject responds to the target, the lower the effort level. Neural outcome measure is the Blood Oxygen Level Dependent (BOLD) contrast during task performance. Explicit and implicit avoidance learning will be assessed using cue ratings assessed after the task, and response reaction times, respectively. Adaptive avoidance learning is defined by higher neural responses, faster reaction times and higher explicit ratings for high relative to low predictive cues. Non-adaptive avoidance learning is defined by larger differential neural responses, reaction times and explicit ratings for the two non-predictive cue dimensions. We will assess whether CFS patients will show increased adaptive and/or non-adaptive avoidance learning compared to healthy controls and whether this normalizes after CBT.

Task independent-neuroimaging will be used to explore alterations in neural networks during rest that may underlie CFS symptoms and CBT effects. A 5 minute resting state scan will be obtained to explore task-independent functional connectivity patterns using a multi echo T2*-weighted, gradient-echo planar imaging (EPI) sequence (TR = 2000 ms, TE = 9.0 ms, flip angle = 90°, voxel size = 3.3 × 3.3 × 3.3 mm, slice thickness: 3.0 mm). During the scan, the room will be completely dark and subjects are asked to lie still with their eyes open to avoid falling asleep.

### Behavioral task

We will use a behavioral version of the moving dot paradigm ([90]; Rahnev et al., [54]) to investigate the influence of expectancy cues on perceptual decisions. Subjects are presented with motion of white dots and are requested to indicate the direction of movement with a button press (i.e. left or right). Moving dots are presented using three coherence levels, determined by subjects’ accuracy level during a preceding training session. Prior to each stimulus subjects are presented with the words “LEFT” or “RIGHT” indicating the direction of motion with 75 % accuracy or with the non-informative word “NEUTRAL”. After each trial feedback is given by changing the colour of the fixation point to green (correct) or red (incorrect). Behavioural outcome measures are the direction of the movement indicated by the participant and reaction times. As described by ([90]; Rahnev et al., [54]), subjects’ hit rates will be used to calculate individual stimulus discrimination sensitivity (d’) and bias towards the cued direction (c). Following Edwards model (see introduction) we will test the hypothesis that CFS patients show a larger bias towards the cued direction compared to healthy controls and whether this changes following CBT.

### Citokines and cortisol

Circulating cytokine concentrations will be determined in blood-plasma using a commercial multiplex assay. Using pax-gene tubes, cytokine mRNA concentrations will be measured. The latter will give more insight into upstream regulation of local cytokine production. Cortisol concentrations will be determined from saliva and hair. We will measure both daily variations of cortisol levels (i.e. cortisol awakening response) in saliva as well as baseline cortisol levels of the past month in hair. Blood and hair samples will be assessed on each test day. Saliva will be collected at home during two consecutive weekdays within two weeks prior to or after each test day. Saliva samples will be taken at 4 different time points during a day: directly after waking, 30 minutes after waking, around 11.00 a.m. or at least 1 hour after the second sampling and around 08.00 p.m. Cytokine and cortisol concentrations will be compared between CFS and HC and before and after CBT or waiting list.

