### Randomization

CFS patients will be randomized to either the CBT condition (66 %) or waiting list condition (33 %). Randomization will take place per patient after the first session day in the presence of the therapist and patient, either during the second diagnostic appointment with the therapist or during a phone call with the therapist. Randomization will be done by supporting staff of the ECCF who are not directly involved in the study. Concealed allocation will be guaranteed by using a central web-based randomization program, developed by an independent statistical advisor. Patients randomized to the intervention group will start treatment directly and will be treated with CBT for CFS (see above). Patients randomized to the control group will start with CBT for CFS 6 months later, after the second assessment. The researchers that will collect and analyze the data are not blind to the allocation, because knowledge of treatment progress is necessary for the planning of the second test day.

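### The saliva window runs two weeks past the first test day, so some baseline salivary cortisol samples may follow disclosed allocation and the first days of CBT

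*Protocol article*

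**What the plan says.** All references are to the protocol article.

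- **Saliva window** (Citokines and cortisol): "Saliva will be collected at home during two consecutive weekdays within two weeks prior to or after each test day". There are four samples a day, the first two at waking and 30 minutes later.
- **Blood and hair** (same section): "Blood and hair samples will be assessed on each test day".
- **Use of the data** (same section): "Cytokine and cortisol concentrations will be compared between CFS and HC and before and after CBT or waiting list". The Study design section calls the first round of biomarker sampling the baseline.
- **Allocation** (Randomization): "Randomization will take place per patient after the first session day in the presence of the therapist and patient". This happens at the second diagnostic appointment or by phone. The interval from the first session day is not given.
- **Start of treatment** (Randomization): "Patients randomized to the intervention group will start treatment directly". Waiting-list patients "will start with CBT for CFS 6 months later, after the second assessment".
- **Content of CBT** (Intervention): 12 to 14 sessions over about 6 months, opening with explanation of the model and goal setting. After that, "patients will learn to regulate their sleep-wake cycle by maintaining fixed bedtimes".
- **Another home measure** (Physical activity): the actometer is worn in the two weeks before each test session only.
- **Consent**: the Ethical aspects section places written consent before the first testing day. The Study population and recruitment procedure section and the Session procedure section place it on that day.

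**The concern.** A baseline used to compare change between randomised arms should be taken before the patient knows her arm and before treatment starts. Blood and hair meet this condition because they are tied to the first test day, which precedes randomisation. Saliva does not have to, because its window stays open for two weeks after that day and no rule closes it at allocation.

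Two things can then enter a baseline sample. One is knowledge of the allocation, which can affect either arm. The other, in the CBT arm only, is the first days of treatment. The measure is anchored to waking, and sleep-wake regulation is an early component of the therapy, so the exposure is relevant to the measure.

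At stake is the cortisol part of the third aim, which asks whether cortisol changes with CBT. The same first-round samples also serve the comparison of patients with healthy controls. If sampling dates are not kept, affected samples cannot be identified afterwards.

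**Working it through.** The plan gives no figure to reproduce here. The check sets the sequence of events against the window and then bounds the dilution.

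**Step 1: order of events.** Let day 0 be the first test day. Saliva is permitted from day −14 to day +14. Allocation falls on day *a* (after day 0, not stated) and CBT starts on day *L*, soon after *a* (not stated). A permitted sample can follow allocation whenever *a* is below 14, and can follow the start of CBT whenever *L* is below 14. Nothing in the article excludes either.

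**Step 2: greatest CBT exposure in a baseline sample.** Maximum exposure = max(0, 14 − *L*) days. The course is taken as 26 weeks = 182 days (about 6 months, Intervention section). *L* is an assumption, varied from 0 to 14.

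**Step 3: dilution of the mean CBT change.** Assume the effect accrues linearly over 182 days. A sample taken *d* days into CBT already holds *d*/182 of the effect, and the measured change loses that fraction. Dilution = (share of CBT-arm baselines taken after CBT start) × (their mean exposure)/182.

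- Pattern A, samples spread evenly over day −14 to +14: share (14 − *L*)/28, mean exposure (14 − *L*)/2, so dilution = (14 − *L*)²/(56 × 182).
- Pattern B, all samples after the test day, spread evenly over day 0 to +14: share (14 − *L*)/14, same mean exposure, so dilution = (14 − *L*)²/(28 × 182). This pattern would arise if consent is given on the first session day and saliva waits for it.

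| *L* (days) | Max exposure (days) | Share of 182 days | Dilution, A | Dilution, B |
|---|---|---|---|---|
| 0 | 14 | 7.7% | 1.9% | 3.8% |
| 3 | 11 | 6.0% | 1.2% | 2.4% |
| 7 | 7 | 3.8% | 0.5% | 1.0% |
| 10 | 4 | 2.2% | 0.2% | 0.3% |
| 14 | 0 | 0% | 0% | 0% |

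If half the samples were taken before the test day and the other half all on day 14, with *L* = 0, dilution would be 0.5 × 14/182 = 3.8%. Only if every CBT patient sampled on day 14 with *L* = 0 would it reach 14/182 = 7.7%, which is not a realistic pattern.

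**Step 4: how much therapy fits.** Evenly spaced sessions fall every 26/14 = 1.9 to 26/12 = 2.2 weeks. Two weeks therefore hold 2/2.2 = 0.9 to 2/1.9 = 1.1 session intervals, or about one session. Explanation and goal setting come first in the described order, so sleep-wake regulation may not have begun when a late baseline sample is taken.

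**Step 5: knowledge of allocation.** This needs only *a* below 14, so it can touch at least as many samples as CBT exposure does, and in both arms. The documents give nothing from which its size or sign could be computed.

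**The case against.** The strongest reply is that the overlap is possible but not shown. Starting directly is relative to randomisation, not to the first test day. If CBT begins 14 or more days after that day, no baseline sample falls within treatment. Day-level scheduling may also sit in the full protocol that the article condenses. The first part stands, and it is why the size is given as a range that starts at zero. The second does not dispose of the point: the article does state a window, and as stated it extends past allocation.

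Two stronger readings are tempting, and the documents support neither.

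- **A large loss of effect.** A reader might suppose that 25 to 50% of CBT baselines follow the start of treatment and that 20 to 50% of the final change is already present, giving 0.25 × 0.20 = 5% to 0.50 × 0.50 = 25% attenuation. That requires a strongly front-loaded response within at most 14 of 182 days, for which the article offers no evidence. Nor can one say that every error shrinks the contrast, since the direction of an allocation-knowledge effect is unknown.
- **A treated waiting-list follow-up.** A reader might infer that the same window lets waiting-list patients give their final sample after starting CBT. Their treatment begins after the second assessment, and the Study design section counts biomarker sampling among the measures gathered at that session. The natural reading is that the assessment includes its saliva. The article does not say so outright, so this merits a clarifying phrase and no more.

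The scope is also narrow. Blood cytokines, hair cortisol, MRI and the primary clinical outcomes do not depend on this window.

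**Conclusion.** The point holds in limited form. The stated window permits first-round salivary cortisol to be taken after a disclosed allocation and, if CBT starts within two weeks of the first test day, up to 14 days into treatment. Those samples are not a true baseline for the CBT versus waiting-list comparison of change.

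Direct dilution of the CBT change is probably about 0 to 4%. This rests on an assumed lag of 0 to 14 days, linear accrual over 26 weeks, and the sampling patterns set out above; a front-loaded response would make it larger. The influence of knowing the allocation cannot be sized or signed from the documents. The case for acting is that the baseline should precede allocation, that the defect cannot be repaired later without sampling dates, and that the correction is cheap.

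**What to change.** In the sampling instructions:

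1. Require both first-round saliva days after written consent and before the allocation call or appointment. First reconcile the consent timing, because the Ethical aspects section differs from the recruitment and Session procedure sections. A rule that all first-round saliva must precede the first session could put research sampling ahead of consent if consent is given on that day.
2. State that the second assessment includes the home saliva, so that waiting-list samples are complete before the first CBT session. This orders the sampling and leaves treatment unchanged.
3. Apply the same window, relative to the test day, to healthy controls.
4. Record each sampling date, together with the dates of allocation and first CBT session.
5. Exclude baseline samples taken after allocation from the main salivary cortisol analysis, or show the results without them.

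The cost is a few sentences of instruction, some date fields, and a few more missing saliva sets where patients miss the shorter window. If allocation follows very soon after the first session, the post-consent window may be tight, which is a further reason to settle the consent wording first. The actometer's pre-session window suggests that home measurement before a visit was considered workable, subject to the same consent question.
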